# Implementing Exercise in Standard Cancer Care (Bizi Orain Hybrid Exercise Program): Protocol for a Randomized Controlled Trial

**DOI:** 10.2196/24835

**Published:** 2021-08-09

**Keywords:** patients with cancer, physical activity, primary care, behavioral change, randomized controlled trial, overall survival

## Abstract

**Background:**

Despite the established benefits of regular exercise for patients with cancer to counteract the deleterious effects of the disease itself and treatment-related adverse effects, most of them do not engage in sufficient levels of physical activity and there is a paucity of data on the integration of efficacious exercise programs that are accessible and generalizable to a large proportion of patients with cancer into routine cancer care.

**Objective:**

We intend to examine the effects attributable to the implementation of a community-based exercise program on cardiorespiratory functional capacity and quality of life for patients with cancer.

**Methods:**

This will be a hybrid study. In the first experimental phase, patients diagnosed with any type of cancer will be randomized into two parallel groups. One group immediately performs Bizi Orain, a 3-month supervised exercise program (3 times a week), in addition to behavioral counseling in a primary health care setting; the other is a reference group that starts the exercise program 3 months later (delayed treatment). In the second observational phase, the entire cohort of participants will be followed-up for 5 years. Any person diagnosed with cancer in the previous 2 years is eligible for the program. The program evaluation involves the uptake, safety, adherence, and effectiveness assessed after completion of the program and with follow-ups at 3, 6, 12, 24, 36, 48, and 60 months. The primary outcomes of the experimental study, to be compared between groups, are improved physical function and quality of life, whereas overall survival is the main objective of the prospective study. To analyze the association between changes in physical activity levels and overall survival, longitudinal mixed-effects models will be used for repeated follow-up measures.

**Results:**

A total of 265 patients have been enrolled into the study since January 2019, with 42 patients from the hematology service and 223 from the oncology service.

**Conclusions:**

Bizi Orain is the first population-based exercise program in Spain that will offer more insight into the implementation of feasible, generalizable, and sustainable supportive care services involving structured exercise to extend survival of patients with cancer, improve their physical function and quality of life, and reverse the adverse effects of their disease and related treatments, thereby reducing the clinical burden.

**Trial Registration:**

ClinicalTrials.gov NCT03819595; http://clinicaltrials.gov/ct2/show/NCT03819595

**International Registered Report Identifier (IRRID):**

DERR1-10.2196/24835

## Introduction

Cancer is one of the diseases that causes major public health problems worldwide. The lifetime probability of developing any type of cancer in Spain is 49.9% in men and 32.2% in women [1]. Currently, increasing incidence rates and decreasing mortality rates due to advances in early detection and treatment have translated to a larger number of people living with cancer. This leads to increased costs of cancer care and a growing burden on health care systems in terms of medical management, cancer surveillance, and supportive care [2].

The disease itself and the treatments used lead to increases in psychosocial distress and depression, impaired cognitive function, increased levels of pain and fatigue, and a significant reduction in cardiorespiratory fitness and strength, as well as muscle (accelerated sarcopenia and cachexia processes) and bone mass losses, alongside increases in body fat. Consequently, patients with cancer have a poor quality of life and a greater risk of developing comorbidities [3].

It has been estimated that 30%-50% of cancer cases are preventable by reducing exposure to modifiable risk factors such as a sedentary lifestyle, poor diet, and excess body fat, and hence, these risk factors have become the target of the global strategy for cancer prevention [4,5]. A growing body of evidence has demonstrated that patients with cancer who achieve the minimum of 150 min·wk^-1^ of moderate or 75 min·wk^-1^ of vigorous physical activity (PA) levels recommended by the American College of Sports Medicine [6] and Australian Association for Exercise and Sport Science [7] experience ~27%-35% lower rates of cancer-related death and recurrence [8]. Current evidence from experimental studies indicates that exercise reduces tumor growth and cancer-specific mortality in a dose-dependent manner [6]. To target tumor intrinsic factors, moderate-to-high intensity endurance exercise is better than light exercise [9]. During exercise, the release of several systemic factors (ie, catecholamines and myokines), sympathetic activation, increased blood flow, shear stress, and increased temperature exert immediate stress on tumor metabolism and homeostasis. Following long-term training, such acute effects lead to reductions in systemic inflammation and oxidative stress, hormone-receptor binding, and adaptations in the modulation of circulating factors (ie, insulin, growth factors, and sex-steroid hormones); they also lead to intratumoral adaptations allowing improved blood perfusion, enhanced immunogenicity, and changes in gene expression and metabolism, which contribute to slower tumor progression and may reduce the ability of cancer cells to form tumors in distant tissues [9,10].

Further, resistance training is particularly important for patients with cancer experiencing loss of muscle mass (ie, sarcopenia or cachexia) during and following treatment [11,12]. This type of training is associated with a 33% lower risk of all-cause death after adjusting for potential confounders, including PA [13].

Despite the established benefits of exercise for patients with cancer and calls to include it as an integral part of cancer treatment, the chances of this information reaching patients are considerably reduced by the self-reported lack of knowledge among oncologists concerning how to properly promote and prescribe exercise [14,15] and paucity of translation strategies for integrating efficacious exercise programs into routine cancer care [16]. Unfortunately, only ~13% of patients with cancer meet international PA guidelines objectively measured with accelerometers [17].

Nonetheless, in recent years, community-based oncological exercise programs have been gaining prominence. LIVESTRONG at the Young Men’s Christian Association (YMCA) [18,19] is a community-based exercise program that has shown sustainable benefits in terms of physical function and self-perceived health. Our previous findings from the “Eficancer” study also indicate that exercising thrice a week during a 12-week individually tailored exercise program conducted at local health centers can improve quality of life and physical function, and these improvements are sustained over time [20].

Exercise program accessibility remains a challenge in implementing the international PA guidelines, but this challenge could be mitigated with strategies and pathways that connect patients with exercise-related resources and a well-designed behavioral intervention program to counteract the common barriers to exercise faced by patients with cancer during and after first-line treatments [21]. Further, the long-term effects on the PA levels, physical function, survival, and cost-effectiveness of large-scale community-based programs that are accessible and generalizable to a large proportion of patients with cancer (ie, administered in a standard supportive care setting) are unknown.

The main objectives of this study are as follows:

to examine the effects attributable to an exercise program on physical function, and quality of life, and adverse effects compared to health habit prescriptions, and to explore whether these effects vary by cancer type, stage and treatments, age, or sexto analyze the association between the actual exercise dose (ie, number of sessions and exercise intensity, objectively measured PA level with accelerometers) and measured outcomesto assess the cost-effectiveness of the program

## Methods

Bizi Orain, which means “live now” in Basque language, is an evidence-based exercise program that adheres to the American College of Sports Medicine guidelines for cancer survivors [6] and is based on the “Life Now” exercise program for people with cancer delivered in Australia [22]. The program is administered by the Primary Care Research Unit of Bizkaia-Biocruces Bizkaia Research Institute (PCRUB-BBRI) and Deusto University and is delivered at a network of health centers equipped with Bizi Orain exercise laboratories integrated into the public health system of the Basque Country (Osakidetza).

### Program Design

Bizi Orain is a hybrid two-stage study. During the first 3 months, the study has a parallel-group randomized controlled clinical trial design, where study participants are randomly allocated (1:1) to either the Bizi Orain exercise program in addition to a previously reported behavioral intervention [23,24] for the promotion of healthy habits, or to the Prescribe Vida Saludable (PVS) group (In Spanish, “Prescribe Vida Saludable” means “prescription of healthy habits”) alone. After the postprogram assessments, participants allocated to the PVS group will initiate the Bizi Orain exercise program. Thereafter, a 5-year prospective observational cohort study will be conducted with follow-ups at 3, 6, 12, 24, 36, 48, and 60 months (Figure 1) to (1) examine the long-term clinical effects of PA exposure on overall survival, physical function, and patient-reported outcomes and (2) evaluate the feasibility of Bizi Orain, identifying potential barriers and facilitators for a generalized and sustainable exercise program within standard health care settings. To address this point, a qualitative research study will be conducted involving clinical, research, administrative, and community staff, and patients with cancer.

**Figure 1 figure1:**
[figure not shown]
Schematic overview of the process for program implementation and evaluation.

### Participants

Participant recruitment will last for 2 years starting from January 2019. People with any diagnosis of cancer currently receiving treatment or diagnosed less than 2 years earlier are eligible to participate and they are referred by their hospital oncologist, hematologist, or primary care general practitioner. To minimize the risk of hazards associated with program participation, patients will be excluded if they meet any of the following criteria: (1) neutropenia: absolute neutrophil count<500 mm^3^; (2) severe anemia: hemoglobin concentration<0.8g/dL; (3) platelet count<50000 μL; or (4) any musculoskeletal, cardiovascular, or neurological disorder that could place the participant at risk of injury or illness resulting from the exercise program (as determined by the patient’s clinician).

Numerous approaches are to be adopted to raise awareness about the program including the following: (1) training for oncology clinicians and support staff to facilitate direct referral of patients; (2) distribution of program flyers at hospitals, cancer centers, and community-based organizations as well as events for health professionals and patients; 3) sending information (by email and post) to people who have contacted the regional cancer association and expressed interest in exercise; 4) advertisements and coverage in local media; and 5) posts on the regional cancer association website and social media accounts. Specifically, the hospital’s Department of Oncology has established a system for identifying eligible patients. The oncologists, hematologists, or primary care general practitioners who have identified eligible patients inform them about the study, invite them to participate, and give them a written informed consent form. Once a patient agrees to participate, the clinicians inform the program administrators, and in the case of the hospital specialists, the patient’s general practitioner. Potential participants are able to self-enroll in Bizi Orain by telephoning the program administrators and by direct referral from their clinician. Eligible patients who agree to participate are invited to the baseline assessments. Participants are included in the study once they have signed the informed consent form and baseline data have been collected.

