#### Adherence

Attendance at health-center–based exercise sessions and the reason for any missed sessions will be tracked throughout the program. Adherence to the recommended amounts of PA for cancer survivors [26] is to be assessed by 7-day accelerometer recordings obtained from a randomly selected subset of the participants. Further, completion of assessments at preprogram and postprogram time points as well as follow-up questionnaires will be reported. Compliance with the Bizi Orain exercise program procedures by exercise physiologists/nurseries at each site will be monitored through evaluation of program documentation (ie, screening, assessment, and exercise prescription documents).

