### Effectiveness: Primary Study Outcomes

#### Physical Function (Clinical)

Physical function is assessed by 400-m walk tests in a 20-m corridor, repeated chair stand tests (5 times), and handgrip dynamometry tests [27-29]. Each participant will perform a graded submaximal cardiopulmonary exercise test (CPET) on an electric braking cycle-ergometer (ergoline GmbH, ergoselect 4) in the laboratory of the University of Deusto in a controlled environment (temperature, ±21 ºC; relative humidity, 50%-55%; barometric pressure, ±720 mm Hg). Briefly, the test protocol involves an unloaded 5-min warm-up followed by 1-min stages with 10-W workload increments from an initial workload of 20 W [30]. Participants will be asked to maintain a steady cadence between 60 to 70 rpm. Gas exchange will be recorded breath by breath using a CPET machine (Geratherm Ergostik). The test is performed until confirmation of at least one of the following criteria: (1) The second ventilatory threshold or the so-called “respiratory compensation point” (RCP) is observed from the Wasserman figures (respiratory equivalents, and O_2_ and CO_2_ partial pressure changes). (2) The respiration exchange ratio (RER)>=1.05 and rating of perceived effort (RPE)>8 on the 0-10–point Borg scale [31]. (3) Participants exhibit volitional exhaustion without meeting the previous criteria.

From a pragmatic viewpoint and owing to the difficulties of performing a CPET in a community-based program setting, the results obtained from the CPET will not be used for individualized prescriptions of exercise intensity during the sessions. However, these results (ventilatory threshold heart rates) will be used to evaluate the actual exercise intensity undertaken by participants when following a standard exercise prescription based on simpler cost-effective methods like RPE and estimated heart rate reserve (HRR).

The maximal strength in the upper and lower body will be measured in terms of the 5-repetition maximum (5RM) (the maximum load that can be lifted five times) in chest and leg press exercises, respectively [32]. These assessments are to be conducted by an independent exercise physiologist not involved with administering the exercise intervention.

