#### Group Exercise Sessions

Exercise sessions twice a week are conducted in groups of approximately 8 participants under the supervision of an accredited exercise physiologist or a nurse in the Bizi Orain exercise laboratories at the local health centers. The sessions last approximately 1-1¼ h and include a combination of moderate-to-high intensity aerobic and resistance exercises. The aerobic exercise component includes 30-35 min of at least moderate-intensity cardiovascular exercise using cycle ergometers and treadmills. The exercise intensity increases from moderate intensity for 8-min periods alternating with 2-min lower-intensity periods during the first month, moving toward higher-intensity 5-min intervals by the third month (Figure 2).

The exercise intensity zones are tailored to each patient by the estimated maximum heart rate using the equation 206.9 – (0.67 × age) [43] and applying specific intensity boundaries based on the HRR, defined as the difference between the resting heart rate and maximum heart rate. The %HRR has been adopted by the American College of Sports Medicine as the gold standard for indirect assessment of exercise intensity [44]. Every exercise session will be monitored with a heart rate monitor, teaching the patients to self-manage their exercise sessions with respect to the prescribed target intensities. The target intensity is between 40% and 85% of the HRR [44]. The perceived level of effort is recorded using the Borg RPE scale from 0 (rest) to 10 (maximal effort) [45], with the target intensity progressively increasing from 3 to 5-6 points (Table 1).

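### The severe-anaemia exclusion limit is printed as haemoglobin below 0.8 g/dL (8 g/L), a value no candidate for this programme could have, so as written the safety criterion excludes nobody.

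*Protocol article*

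**What the plan says.** The Participants section of the protocol article introduces its exclusions as a safety measure: "To minimize the risk of hazards associated with program participation, patients will be excluded if they meet any of the following criteria". Four criteria follow: a neutrophil limit of 500, a haemoglobin limit, a platelet limit of 50000, and a clinician-judged exclusion for musculoskeletal, cardiovascular or neurological disorders. The haemoglobin criterion is "severe anemia: hemoglobin concentration<0.8g/dL".

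Three other parts of the article show what an enrolled patient then does:

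- Physical Function (Clinical): "Physical function is assessed by 400-m walk tests in a 20-m corridor", and "Each participant will perform a graded submaximal cardiopulmonary exercise test (CPET) on an electric braking cycle-ergometer".
- Group Exercise Sessions: "The target intensity is between 40% and 85% of the HRR".
- Program Design: after the 3-month assessments, "participants allocated to the PVS group will initiate the Bizi Orain exercise program". Both arms are therefore offered the training.

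On who applies the criteria, the Participants section says of eligible patients that "they are referred by their hospital oncologist, hematologist, or primary care general practitioner". It also lets potential participants enrol themselves by telephone.

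**The concern.** A haemoglobin limit labelled severe anaemia should separate patients who may safely exercise from those who may not. A limit of 0.8 g/dL cannot do this, because everyone who could attend the baseline assessment lies above it.

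The criterion matters in this population. Patients may be under active treatment, and some come from the haematology service (42 of 265 enrolled according to the Abstract; 19 of 123 according to the Results section). Low haemoglobin at screening is therefore foreseeable. Every participant takes the graded exercise test, and both arms go on to moderate-to-high intensity training. A screener or another site working from the published text would have no usable limit.

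There is a second, conditional consequence. The Adherence section says that sites' compliance with programme procedures "will be monitored through evaluation of program documentation (ie, screening, assessment, and exercise prescription documents"). If the screening documents repeat the printed figure, and if that review covers eligibility, it could not flag any patient for anaemia. Those documents are not shown, so this remains a possibility only.

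**Working it through.** **Inputs.** The printed limit, 0.8 g/dL, comes from the Participants section. The conversion is 1 g/dL = 10 g/L. The intended limit is not in the article; 7, 8 and 10 g/dL are assumed here to show a range, with 8 g/dL the likeliest.

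**Step 1: convert the printed limit.** 0.8 g/dL × 10 = 8 g/L.

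**Step 2: compare the number with its label and with the tests.** A haemoglobin of 8 g/L is not compatible with walking 400 m or pedalling a graded ergometer test. This is general physiology and depends on no cited source. Read literally, the criterion excludes nobody. A patient at an illustrative 6 g/dL, which is 6 / 0.8 = 7.5 times the printed limit, would pass it.

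**Step 3: size of the error.** Factor = intended / 0.8; printed limit as a share of the intended one = 0.8 / intended.

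| Assumed intended limit | Factor too low | Printed limit as share of intended |
|---|---|---|
| 7 g/dL | 7 / 0.8 = 8.75 | 0.8 / 7 = 11.4% |
| 8 g/dL | 8 / 0.8 = 10 | 0.8 / 8 = 10.0% |
| 10 g/dL | 10 / 0.8 = 12.5 | 0.8 / 10 = 8.0% |

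A factor of exactly 10 is what a misplaced decimal point would produce. The conclusion does not depend on which value was meant.

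**Step 4: look for anything in the article that repairs it.** Haemoglobin and anaemia are mentioned nowhere else. The fourth exclusion leaves room for clinical judgement, but only for musculoskeletal, cardiovascular and neurological disorders. The Individual Consultations section describes a one-on-one health-status screening without a haemoglobin limit. The figure stands in running text, and nothing suggests a redaction or a broken table.

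**The case against.** The strongest reply is that this is a self-revealing misprint. The words severe anaemia stand beside the number, and no oncologist, haematologist or general practitioner would take 0.8 g/dL for a working limit. The neutrophil and platelet limits in the same sentence also lack the 'per' in their units, which points to careless printing and not to a badly chosen threshold. The binding eligibility text is in the ethics-approved protocol, of which the article is a condensed account. Other protection exists: clinician referral, the oncology department's system for identifying eligible patients, the initial consultation, supervised and heart-rate-monitored sessions, adverse-event reporting and safety monitoring by the coordination committee. Finally, the sentence on reviewing programme documentation concerns how staff deliver the programme and may not cover blood counts at all.

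Much of this stands. It is very probably a misprint, the safeguards are real, and the documentation argument is conditional on papers not shown and on one reading of that sentence. It should carry little weight.

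The central point survives. The neutrophil and platelet limits remain usable despite their notation; the haemoglobin limit does not. Seeing that 0.8 is wrong does not tell the reader whether 7, 8 or 10 g/dL applies, and none of the safeguards supplies a number. Adverse-event reporting and committee monitoring act only after enrolment. Because self-enrolment is allowed, the article does not make clear that a clinician applies a sensible limit in every case.

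**Conclusion.** The concern holds. The printed haemoglobin limit is wrong and, taken literally, the criterion has no effect. If 8 g/dL was meant, it is too low by a factor of 10; over the assumed 7 to 10 g/dL it is too low by 8.75 to 12.5. The finding rests on the unit conversion, on ordinary physiology and on the absence of any other limit in the article. The intended value is an assumption for the clinical team to confirm.

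The consequence is confined to eligibility and safety. Sample size, power, alpha, randomisation and the analysis are untouched. Nothing in the article shows that any patient was wrongly enrolled. It should be corrected because it is an operative safety threshold and not a slip in background text.

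**What to change.** 1. Check the haemoglobin limit in the ethics-approved protocol and in the screening documents used at the sites.
2. Correct the value or unit in the second exclusion criterion of the article, giving both units. The probable wording is <8 g/dL (80 g/L), subject to confirmation by the clinical team.
3. Only if the approved protocol or screening documents also carry 0.8 g/dL, amend them and review the haemoglobin records of patients already enrolled against the corrected limit.

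The certain cost is one corrected line in the article. The amendment and record review arise only under step 3. No analysis or sample-size work is needed.
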